# The effect of the leisure activities based on chess and cards for improving cognition of older adults: study protocol for a cluster randomized controlled trial

**DOI:** 10.1186/s13063-023-07528-1

**Published:** 2023-07-29

**Keywords:** Leisure activities, Cognitive function, Promotion campaigns, Chess and cards

## Abstract

**Background:**

With the increase in age, the probability of cognitive impairment in the older people is increasing. More and more evidence shows that participating in leisure activities, especially chess and cards, is beneficial to the cognition and mental state of the older people. But the evidence for causal inference is limited. There is a need to conduct a fully powered randomized controlled trial (RCT) and long-term follow-up to test the effectiveness of intervention measures in improving cognitive function and mental state. This paper describes the methodology of a cluster RCT designed to determine the effect of chess and cards leisure activities on the cognitive function of the older people over 60 years old.

**Methods/design:**

A cluster RCT consisting of 8 clusters will be conducted in four regions of Ningxia, China (Helan, Litong, Qingtongxia, and Shapotou). Clusters will be randomly assigned to the advocacy intervention group, which is also delivered with free leisure activities tools (chess and cards), or the control group. A baseline survey will be conducted before the intervention. A mid-term and final survey will be carried out twelve and twenty-four months after the intervention, respectively. The primary outcome is a change in cognitive function, and the secondary outcomes are changes in anxiety, depression, and loneliness.

**Discussion:**

The results of this RCT will be helpful to (1) confirm the effectiveness of chess and cards leisure activities in improving the cognitive function of the older people over 60 years old; (2) determine the relationship between the frequency and duration of chess and cards leisure activities and cognitive function; (3) provide evidence of promoting participation in leisure activities through education campaigns and free provision of chess and cards tools; and (4) provide valuable information for successful aging.

**Trial registration:**

Chinese Clinical Trial Registry: ChiCTR2200066817. Registered on 19 December 2022.

**Supplementary Information:**

The online version contains supplementary material available at 10.1186/s13063-023-07528-1.

## Background

Driven by increased life expectancy and declining fertility rates, we are moving towards an aging world. Aging is not only the aging of the body and the degeneration of physiological functions, but also the decline of psychological and cognitive functions [1]. In the absence of effective treatment, the global financial and social burden caused by cognitive decline is set to rise [2].

According to severity, the cognitive decline of the older people can be divided into normal cognitive decline, subjective cognitive impairment, mild cognitive impairment (MCI), and dementia with age [3]. Dementia is the most severe level of impairment, which relieves symptoms but not cures [4, 5]. Interestingly, compared with dementia, the course of MCI is not always linear [6], and its outcome includes returning to normal aging, stabilizing, or progressing to dementia [7–10]. Thus MCI was considered the most effective period for dementia prevention and intervention [11–13].

To date, there are many clinical trials on the pharmacological and non-pharmacological treatment of MCI, but there is still no clear consensus on its treatment. The latter has the advantages of low cost, convenient implementation, and fewer adverse reactions. It has become the primary treatment recommended by clinics and a research hotspot in this field.

Leisure activities are defined as the voluntary use of free time for activities outside of daily life, which is one of the key components of a healthy lifestyle. After retirement, leisure time occupies most of the daily life of the older people. In recent decades, more and more attention has been paid to the role of leisure activities as a protective factor against cognitive function in the older people. A recent study shows that participating in leisure activities, not only as a prevention strategy, but even as an intervention in later life, may promote better cognitive performance through compensation or neural efficiency mechanisms [14]. The potential mechanism for the protective effect of leisure activities on cognitive function is still unclear. Most studies use the cognitive reserve hypothesis to explain the beneficial effects of leisure activities on cognitive function in old age. Increasing the function or plasticity of related neural networks may delay the onset of dementia or reduce cognitive decline, according to the cognitive reserve hypothesis [15].

A systematic review and meta-analysis [16] revealed that the active participation of the older people in leisure and recreational activities, especially intellectual activities, such as reading, playing chess and cards, can improve cognitive reserve, protect and restore cognitive function, and help reduce the risk of dementia in the older people. In addition, some studies have also shown that stimulating intelligence more frequently (such as cards, chess, mahjong, and crossword puzzles) was related to reducing the risk of dementia [17–19] and there may be a dose–response relationship. The reason why these stimulating intellectual games can reduce the risk of dementia may be that playing cards and chess, which involves attention, reasoning, memory, and initiative in cognitive fields, is a powerful and comprehensive stimulating activity for the brain [20, 21].

Meanwhile, playing chess and cards is group entertainment, which not only plays a positive role in cognitive function, but also promotes communication and provides significant social support and emotional comfort for the older people [22, 23]. Studies have shown that cards-playing activities can promote the mental health of middle-aged and older people by providing social communication and interaction [24].

Although previous studies have provided a great deal of epidemiological reference information about the association of leisure activities with cognitive function, the epidemiological evidence linking specific leisure activities with reducing cognitive decline is not enough to indicate whether these activities have any direct preventive or delaying effects. So far, the evidence from randomized controlled trials supporting the cognitive benefits of leisure activities in the older people through chess and cards is still limited. Most research designs are cross-sectional studies [25] or longitudinal studies [26], and causal inferences cannot be made. Individual randomized controlled trials with a small sample size on cognitive leisure activities are limited to cognitive impairment samples [27, 28]. Therefore, intervention research is needed to prove the causal relationship between chess and cards leisure activities and cognitive function in the population, and to verify whether chess and cards leisure activities are an effective non-drug treatment for the older people. In recent years, social media have been a source of information about cognitive impairment prevention and treatment. This is because massive promotion campaign is also one of the most important aspects of health work. We expect the elderly to voluntarily give up problematic living habits and adopt active lifestyles to delay the decline of cognitive function after being advertised.

Furthermore, there is no single, large-scale, and robust design study to measure the cognitive intervention effect of free chess and cards leisure activities on the older people. To solve this problem, we designed a more convenient and economical cluster randomized controlled trial to avoid contamination and evaluate the real effect of the intervention. We aim to maximize the potential health benefits of chess and cards activities for the older people through intervention. We will not only pay attention to communication campaigns, but also the availability of tools (chess and cards), and improving the activities and atmosphere.

We hypothesize that compared with the older people in the control group without any intervention, the long-term collective leisure activities of chess and cards for the aging population can not only promote the older people to maintain a good daily emotional state, but also effectively avoid or prevent the cognitive decline of the older people. In addition, this kind of activity is simple and popular among the older population, and is easy to be implemented among the older people. If the hypothesis is true, it means that preventive intervention for the alterable lifestyle of the older people can improve the clinical manifestations of cognitive impairment in the older people and delay the onset of dementia syndrome, thus contributing to the healthy aging of the brain, which has great public health significance.

### Objectives

This study determined the long-term effectiveness of chess and cards leisure activities in improving cognitive and psychological status in older adults compared with those who did not pursue these activities.

#### Primary objective

To investigate the effects of leisure activities using chess and cards entertainment tools on objectively measured cognitive function compared to usual practice at 24-month follow-up.

#### Secondary objectives

To investigate the impact of intervention over the medium (assessed at 12 months) and long term (assessed at 24 months) on:Cognitive functionPsychosocial variables (anxiety, depression, and loneliness)Frequency and duration of chess and cards activitiesDaily activity functionKnowledge of cognitive impairment prevention

### Trial design

Two years will be spent on this cluster-randomized controlled study. Participants in this study will be older people over 60 years old. It is hypothesized that chess and cards leisure activities can delay cognitive decline, improve neuropsychiatric symptoms of depression, anxiety, and loneliness, and enhance health.

## Methods: participants, interventions, and outcomes

### Study setting

This study is a two-arm, open-label randomized trial and will be conducted in the Ningxia Hui Autonomous Region of China. The recruitment of observation objects is expected to be completed in June 2023. This study protocol follows the standard protocol for clinical trials in accordance with the SPIRIT 2013 statement [29] and follows the CONSORT statement for clinical trial transparency [30]. A flow diagram is provided in Fig. 1 which clearly outlines the study’s recruitment process. The study is registered on the Chinese Registry of Clinical Trials platform under the license ChiCTR2200066817. Research design and consent have been approved by the Ethics Committee of Ningxia Medical University (No.2022–025). Figure 2 shows the design flow chart for this study.

**Fig. 1 Fig1:**
[figure not shown]
Schedule of enrollment, interventions, and assessments for this study

**Fig. 2 Fig2:**
[figure not shown]
Flow chart of the study design

### Cluster and participant recruitment

The study areas are selected by an expert consultation method. First, we selected Helan County of Yinchuan, Litong District of Wuzhong City, Qingtongxia City, and Shapotou District of Zhongwei with high-quality public health work to carry out this study. In the second stage of sampling, taking villages as the basic unit, two villages are randomly selected from the eligible villages in the above four project research areas, and the selected villages are matched (1:1) as control villages and intervention villages respectively. The matching principle is based on the county to which the village belongs.

The selected villages need to meet the following conditions:The population aged 60 is ≥ 100.Residents have fewer daily leisure activitiesVillage cadres/village doctors are serious and responsible.

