#### Demographic

During their baseline visit, we obtained the following covariates from face-to-face interviews: age, sex, education level, living conditions (living alone or with others), family relations, and monthly income. In addition, participants will report previous illnesses (such as hypertension and diabetes) and a family history of dementia. At each follow-up, participants will be asked if there has been any change in these areas. If yes, it will be revised and the latest follow-up information will be used.

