### Sample size

PASS 15.0 software calculated the sample size. Power calculation indicated that with a sample size of 4 clusters in each group and 100 observed objects in each cluster, this study would have 88% power to detect the change in cognitive function with a mean of 1, a standard deviation of 2, and a two-tailed significance level of 5%. As a result of the correlation coefficients being set to 0.050 within clusters, and the coefficients of variation being set to 0.650, four clusters in each group, resulting in a total of 800 people to be recruited. The power of RCT over 80% is considered acceptable [41], so the sample size calculated in this study will be eligible.

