### Assignment of interventions: allocation

#### Sequence generation

In this cluster randomized controlled trial (RCT), 8 villages will be recruited. A village is a cluster. To reduce contamination risk, clusters will be randomized at the village level. Using a computer-generated list, statisticians at Ningxia Medical University randomly assigned villages (clusters) to one of the two groups and stratified them according to the counties to which villages belong before allocation. The randomization will be performed using a computer-generated randomization table in Microsoft Excel.

Randomization will be carried out after the cluster completes the baseline measurement. These clusters will be recruited from Helan County, Litong District, Qingtongxia City, and Shapotou District in Ningxia, China. Our goal is to recruit 800 over-60 s in 8 clusters. Clusters will be randomly assigned to accept one of the following conditions: (1) intervention groups that distribute leisure activities tools (chess and cards) free of charge and promote them, or (2) control groups (routine).

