### Statistical methods

#### Primary and secondary outcomes

The primary purpose of the analysis was to investigate the effects of multicomponent interventions (targeted promotion campaigns, providing free cards and chess leisure activities tools) on objectively measured cognitive function and neuropsychiatric state, compared with the usual practice at 24-month follow-up.

The primary outcome analysis is powered to detect a significant difference in cognitive function and neuropsychiatric status in the older people over 60 years at the end of a 24-month follow-up period. Linear multilevel models will be used to analyze the cognitive function and other neuropsychiatric indicators as outcome variables. Levels indicate the clustering of residents within villages. We take the randomly divided classification variables as independent variables (the intervention group will be compared with the control group), and age, family history of dementia, baseline value, smoking, drinking, and sleep quality as confounding factors. In these linear multilevel models, village clusters will be included as a random effect to simulate the heterogeneity of residents in villages. The model will use restricted maximum likelihood estimation.

After the survey, the differences in baseline characteristics between participants who completed the whole survey and those who dropped out of the study will be compared. Multiple interpolation and sensitivity analyses of missing data are carried out to evaluate the influence of missing data on the obtained results. The effect size of the protocol will be determined by the subjects who participated in the study and completed follow-up. Secondary outcomes measured at other time points will be analyzed using similar methods. In addition, we will use repeated measurement variance analysis to evaluate the changes in the main outcome indicators of each protocol at each time point. Subgroup analyses are planned for baseline characteristics that might affect the primary outcomes.

The p values of all tests are two-sided and the test level α is 0.05. Estimates will also be reported with a 95% confidence interval.

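### Allocation is balanced on county only and the primary model omits education and baseline chess-and-cards play, so a chance gap in either between 4 and 4 villages goes uncorrected

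*Protocol article*

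**What the plan says.** **Selection and pairing (Protocol article, Cluster and participant recruitment).** Two villages are drawn at random from the eligible ones in each of four areas, and "the selected villages are matched (1:1) as control villages and intervention villages respectively". County is the only matching factor: "The matching principle is based on the county to which the village belongs". All villages must also meet three common conditions: enough older residents, few daily leisure activities, and conscientious local cadres or doctors.

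**Allocation (Sequence generation).** The statisticians "stratified them according to the counties to which villages belong before allocation". On timing: "Randomization will be carried out after the cluster completes the baseline measurement". No other balancing factor is named.

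**Baseline data.** The Demographic section lists "age, sex, education level, living conditions (living alone or with others), family relations, and monthly income". The section on self-reported activities adds the frequency and duration of chess-and-cards play, and the Outcomes section places the frequency of leisure activities among the measurements made at baseline, 12 and 24 months.

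**Analysis (Statistical methods, Primary and secondary outcomes).** The linear multilevel model has a random village effect and takes "age, family history of dementia, baseline value, smoking, drinking, and sleep quality as confounding factors". Education and baseline play are not in that list.

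**The concern.** Eight villages are too few for randomisation to balance village characteristics reliably. A county pair removes only what the two villages owe to their county. Whatever else differs, such as schooling or the habit of playing cards, falls to one arm or the other by four coin tosses.

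The baseline value, being in the model, deals with much of a starting gap in cognition itself. Education and prior play have no such protection. Education may be related to how cognition changes over 24 months, and prior play is the behaviour that the intervention sets out to raise. If the arms start apart on either, a reader of the results cannot separate that from the effect of the intervention, and the plan has no stated adjustment to fall back on. Choosing one after the results are seen would be less convincing.

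**Working it through.** The plan gives no figure for expected balance, so there is none to reproduce here.

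**1. Inputs.** From the Sample size section: "4 clusters in each group and 100 observed objects in each cluster" and a within-cluster correlation of 0.05. That correlation was set for the change in cognitive function; using it for a baseline variable is an assumption. An ICC of 0.2, for a more clustered variable such as schooling, is also an assumption, as is the share *c* of between-village variance that county explains (0 or 0.5). Villages are taken as equal in size. The 0.25 SD threshold is chosen here as a visible gap.

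**2. Number of allocations.** There are four counties with two villages each, and one of each pair goes to each arm: 2^4 = 16 allocations, in 8 mirror pairs.

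**3. Chance gap in one variable, in SD units.** Leaving out the county part, which cancels within a pair, a village mean has variance v = ICC × (1 − c) + (1 − ICC)/100. The arm difference is the mean of four within-county differences, each with variance 2v, so its SD is √(2v/4) = √(v/2). The probability of a gap above 0.25 SD is 2 × [1 − Φ(0.25/SD)].

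| ICC | c | v | SD of arm difference | P(gap > 0.25 SD) |
|---|---|---|---|---|
| 0.05 | 0 | 0.0500 + 0.0095 = 0.0595 | 0.172 | 14.7% |
| 0.05 | 0.5 | 0.0250 + 0.0095 = 0.0345 | 0.131 | 5.7% |
| 0.2 | 0 | 0.2000 + 0.0080 = 0.2080 | 0.322 | 43.8% |
| 0.2 | 0.5 | 0.1000 + 0.0080 = 0.1080 | 0.232 | 28.2% |

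At an ICC of 0.01 with no county effect, the figure is only 1.2%.

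**4. What such a gap could do to the estimate.** If one SD of the omitted variable goes with r SD of the outcome after the planned adjustment, a 0.25 SD gap shifts the estimate by 0.25 × r SD. With the plan's SD of 2, that is 0.5 × r points. The documents give no r. Even r = 1 would give 0.5 points, half the target difference of 1, and any smaller r gives proportionately less.

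**5. What screening the allocations would gain.** Simulation: for each simulated trial, score the 16 allocations, keep the best 8 and draw one.

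- One balancing variable, no county effect: P(gap > 0.25 SD) falls from 14.7% to about 0.2% at ICC 0.05, and from 44% to 10% at ICC 0.2.
- Three independent variables scored together (standardised sum of squares), no county effect: from about 15% to about 3% at ICC 0.05, and from about 44% to 28% at ICC 0.2.

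The second line is the relevant one, because cognition, education and play would be balanced together.

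**6. What screening would cost.** The smallest two-sided p of an exact randomisation test rises from 2/16 = 0.125 to 2/8 = 0.25. With three variables, in about 36% of simulated trials the 8 kept allocations always put some two villages from different counties in the same arm, or always in opposite arms.

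**The case against.** The strongest reply is that nothing here is an error. Stratifying by county is a recognised form of restricted randomisation, and screening on covariates is a refinement that a trial may reasonably do without. Chance imbalance is not bias either: over all allocations the estimate is centred correctly, and the random village effect is there to carry such variation. A reader might infer that the arms will be biased, or the trial invalid. The documents do not support that.

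Three further replies also stand:

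- **Baseline cognition is covered.** The variable most likely to matter is already in the model.
- **The villages share more than a county.** The common eligibility conditions, above all the one on few leisure activities, should narrow the spread in prior play.
- **Screening is not free.** A reader might infer that it costs nothing and nearly abolishes imbalance. The near-abolition belongs to one balancing variable at ICC 0.05. With three variables a strongly clustered one still exceeds the threshold in 28% of draws. Fewer allocations remain and some villages become tied. The higher floor for an exact p matters little, since no exact test is planned and 0.125 is already above 0.05.

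It is also not certain that all baseline data would be in hand at the draw. The timing sentence speaks of one cluster completing its baseline, which leaves open whether all eight finish before any is allocated.

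None of this answers the narrower point that education and baseline play are collected but used neither in allocation nor in the stated adjustment.

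**Conclusion.** The concern holds in a limited form. County is the only factor balanced, and the primary model leaves out education and baseline chess-and-cards play. Sex and income are omitted too, but the case is clearest for these two. For one such variable, a chance gap above 0.25 SD has a probability of about 15% at ICC 0.05 and 44% at ICC 0.2 with no county effect, or about 6% and 28% if county explains half the clustering. These figures rest on equal villages of 100, on ICCs that the plan does not give for baseline variables, and on an assumed county share.

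This is a worthwhile improvement, not a flaw that undermines the trial. The model change is close to free and stands by itself. Screening is an optional refinement with modest gains and a named price.

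**What to change.** **Main change.** Add education and baseline chess-and-cards frequency as individual-level covariates in the primary multilevel model, and fix this before any outcome is analysed. Use the baseline records, not values updated at follow-up, because later play is what the intervention is meant to change. The cost is one line in the plan and two more coefficients estimated from about 800 people. Individual-level covariates do not draw on the few between-village degrees of freedom (8 − 2 = 6) as village-level ones would. They will not remove an effect that acts only through the village as a whole.

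**Optional change.** This is open only if all eight baselines are complete before any village is allocated; the recruitment dates in Trial status suggest that the time for it may have passed. List the 16 within-county allocations and score each on the arm difference in baseline cognition, education and play. Drop the worst-balanced, keep mirror allocations together so that each village retains a 1/2 chance of either arm, and draw one by computer. Check that no two villages from different counties are always together or always apart, and relax the cut-off if they are. Keep the balancing variables in the model. The cost is a short program, waiting for the last baseline, and fewer allocations.
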